### Outcomes

The primary outcome for the trial is a previously tested and validated team measurement score that consists of 31 questions, asking the respondent to answer “agree” or “disagree” on a four point scale that is converted to a 100 point score per methods referenced in Stock et al. [15]. The team measurement score focuses on four elements of team behavior: communication, roles and goals, cohesion, and team primacy. Responses from each team member will be used to generate an overall score for the team.

Secondary aims include patient satisfaction assessed through Press Ganey ® Medical Practice surveys. These surveys are implemented routinely within the health-care system. After a patient has had an appointment, if they are randomly selected, the survey is sent to them within 30 days for completion. A random sample of each team’s assigned patients that had a recent appointment were surveyed by Press Ganey® every quarter and reported at the site, care team, and provider levels. Patients’ responses are de-identified so that we know who provided the care but not to whom. We receive the percentage of patients who rated their provider with a top score for a given quarter. We monitor the quality outcomes in chronic disease management and prevention to ensure safety and an adequate quality of care are provided in both the control and intervention arms. Quality metrics at the care team level are assessed monthly for diabetes, depression, asthma, hypertension, and vascular issues. The metrics are calculated as the number of patients who met the quality criteria divided by the number of patients who are assigned to the care team who qualify for the assessment. The criteria for each metric are set by Minnesota Community Measures [16].

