### Allocation

Groups of teams or a team were randomized in a 1–1 allocation between the intervention and control groups. The groups were balanced across type (primary care internal medicine, family medicine, and pediatrics) and panel size (large vs. other). A computer algorithm accessed by the study statistician randomized the groups using dynamic allocation [17]. Blinding did not occur.

Concerns about contamination did not allow for randomization at the care team level as staff within a care team could overlap with other sites and other care teams within a site. After recruitment had completed, the study team statistician assessed the staff overlap and grouped the teams based on this to ensure that each unit of randomization was unique.

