### Statistical methods

All teams will be analyzed in the arm to which they were assigned using techniques appropriate for pragmatic cluster randomized trials. Baseline characteristics will be summarized at the site and care team levels within each trial arm, to provide counts and frequencies for categorical variables and means with standard deviations and ranges for continuous variables. We will test the null hypothesis of no difference between arms in baseline characteristics using *t*-tests and chi-square tests adjusted for clustering by care team.

To account for the effects of care team clustering, we will use hierarchical generalized linear models with random main effects specified at the care team level. Such models are appropriate for analyzing cluster randomized trials and will allow us to account for any imbalances in care team characteristics across study arms. For measures collected from the team members, the outcome of interest will be the 6-month post-baseline responses, adjusting for baseline responses. If there are differences in baseline characteristics between the two study groups, these will be accounted for using hierarchical generalized logistic or linear regression models that include an indicator for study arm.

For outcomes collected at the care team level (patient satisfaction and quality measurements), the percentage of patients who gave the top score for satisfaction and the percentage of patients who met the quality criteria will be compared between arms without accounting for clustering effects, as the data are not available at the individual level.

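### Patient satisfaction and quality of care are exempted from any allowance for clustering on a mistaken ground; team-level percentages are enough to analyse these outcomes by randomised unit

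*Protocol article*

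**What the plan says.** The Statistical methods section opens by promising to analyse all teams as assigned, "using techniques appropriate for pragmatic cluster randomized trials". Staff survey outcomes get hierarchical models with a care-team random effect. The section then turns to a second class: "For outcomes collected at the care team level (patient satisfaction and quality measurements"). For these, the percentages "will be compared between arms without accounting for clustering effects, as the data are not available at the individual level".

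The Outcomes section describes the data. For satisfaction: "We receive the percentage of patients who rated their provider with a top score for a given quarter". These results are "reported at the site, care team, and provider levels". For quality: "Quality metrics at the care team level are assessed monthly for diabetes, depression, asthma, hypertension, and vascular issues". Each metric is a ratio: "The metrics are calculated as the number of patients who met the quality criteria divided by the number of patients who are assigned" to the team and qualify for the assessment.

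The Allocation section says that groups of teams, or single teams, were randomised. The statistician assessed staff overlap and "grouped the teams based on this to ensure that each unit of randomization was unique". The Trial status section gives 11 units (13 care teams) in the intervention arm and 11 units (16 care teams) in usual care.

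**The concern.** The article fixes a rule and gives a reason for it, so this is more than a detail left to an analysis plan. The reason does not support the rule. Lack of patient-level records rules out a model with patients as rows. It does not rule out a comparison of cluster summaries, which needs only aggregate data and the identity of each cluster, and both are available here.

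The sentence also leaves the analysed row undefined. If it is the care team, team-level clustering is already handled, so the statement that clustering is ignored misdescribes the analysis, and what remains unhandled is the grouping of teams into randomised units. Teams were grouped because they share staff, so some correlation within a unit is plausible.

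Improved patient satisfaction and outcomes are part of the stated objective, and quality is also monitored to check that care is adequate in both arms. A test that is too liberal on these outcomes could present ordinary variation between units as an effect of the intervention.

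**Working it through.** **The plan's own figure.** The article gives no figure for satisfaction or quality. Its Sample size section covers continuous outcomes in general: 10 clusters per arm, intra-cluster correlation (ICC) 0.05, two-sided alpha 0.05. With 10 individuals per cluster the design effect is 1 + 9 × 0.05 = 1.45, and the effective size per arm is 100/1.45 = 69. Power for 0.5 SD is 79.3% (noncentral t, 18 df), which agrees with the stated 80%. So the planning allowed for clustering.

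**Inputs.** From the article: 13 teams in 11 units against 16 teams in 11 units. (The count after withdrawals is not fully clear in Trial status; the stated split is used.) Assumed, because the article gives none for these outcomes: correlation between teams of one unit, patients per team, patient-level ICC, and correlation between months.

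**A. One percentage per team (the natural reading).** With N teams in an arm, unit sizes n_i and within-unit correlation ρ, the variance of the arm mean is inflated by 1 + (Σn_i²/N − 1)ρ. The unit sizes are not given, so two layouts bracket them.

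- *Extra teams spread out.* Intervention: 9 single teams and 2 pairs, Σn² = 17. Usual care: 6 single teams and 5 pairs, Σn² = 26. At ρ = 0.5 the factors are 1.154 and 1.3125. The variance ratio is (1.154/13 + 1.3125/16)/(1/13 + 1/16) = 0.1708/0.1394 = 1.225. Type I error = 2[1 − Φ(1.96/√1.225)] = 7.7%.
- *All extra teams in one unit per arm.* Σn² = 10 + 3² = 19 and 10 + 6² = 46. At ρ = 0.5 the factors are 1.231 and 1.9375, the variance ratio is 0.2158/0.1394 = 1.548, and the type I error is 11.5%.

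Simulated t-tests on the 29 team percentages agree:

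| ρ within unit | Spread | All in one unit per arm | t-test on unit means, 11 v 11 |
|---|---|---|---|
| 0 | 5.0% | 5.0% | 5.0% |
| 0.2 | 6.0% | 7.5% | 4.9% |
| 0.5 | 7.8% | 11.4% | 5.0% |
| 0.8 | 9.5% | 15.6% | 4.8% |

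The last column uses aggregate percentages only and holds the nominal level throughout.

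**B. Readings the text does not state, for scale.**

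- *Patients pooled by arm.* Design effect 1 + (m − 1) × ICC; type I error 2[1 − Φ(1.96/√DE)]. With m = 30 and ICC 0.01, DE = 1.29 and the error is 8%. With m = 100 and ICC 0.01, DE = 1.99 and the error is 17%. With m = 500 and ICC 0.05, DE = 25.95 and the error is 70%.
- *Monthly values of a team treated as independent rows.* For within-team correlations of 0.3 to 0.8, simulation gives 22% to 40% with 6 months and 35% to 54% with 12.

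**The case against.** The strongest defence is that the sentence is only clumsy. The outcomes are introduced as collected at the care-team level, and a percentage is compared. With one percentage per team there are no patient rows for a team random effect to act on, and the remark about individual data may mean no more than that. The comparison is then already cluster-level, and simulated type I error is 4.6% to 5.2% when teams are independent. The article implies that most units are single teams, the outcomes are secondary, and the primary outcome has a hierarchical model.

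Most of this stands, and it sets the size of the point. A reader might infer from the words about ignoring clustering that these p-values will be far too small. The article does not support that. It nowhere says that patients will be pooled by arm, and for satisfaction it mentions only percentages received, with no counts to pool. It gives monthly assessment as a frequency of measurement and does not make the month the row of analysis. How months or quarters are summarised can reasonably be left to an analysis plan.

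Two things survive the defence. The stated reason is wrong on any reading, and the sentence contradicts the opening of its own section. Even on the benign reading, the grouping of teams into randomised units is ignored, and the level is 5% only if teams that share staff are uncorrelated.

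**Conclusion.** The concern holds in a limited form. The exemption is wrong as written: aggregate data are enough for a valid cluster-level analysis, and the rule conflicts with the promise to use methods suited to cluster trials.

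On the natural reading the true type I error at a nominal 5% is about 5% to 12% for within-unit correlations of 0 to 0.5, and up to about 16% at a correlation of 0.8 with all extra teams in one unit per arm. These figures rest on the stated 13/16 team split, assumed correlations and assumed unit sizes.

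The larger ranges (about 8% to 70% with pooled patients, about 20% to 55% with 6 to 12 monthly values as independent rows) show what the loose wording would permit. They are not what the article says will be done. Only secondary outcomes are affected. Severity: should be fixed.

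**What to change.** Delete the exemption and name the randomised unit as the unit of analysis for satisfaction and quality.

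- **Main analysis:** compare one summary percentage per randomised unit over the follow-up window, 11 against 11, on 11 + 11 − 2 = 20 degrees of freedom. Weight by denominator where counts are held. Team summaries with a random effect for randomised unit are an equivalent choice.
- **Quality:** adjust for the pre-period value. The article already collects these metrics from 6 months before the start of the study. If team-level numerators and denominators are held, a binomial mixed model with unit and team effects is an option.
- **Satisfaction:** if only percentages are received, use one summary per unit, weighted by survey count only where the count is available.

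The cost is a change of wording, modest programming, and somewhat wider intervals for secondary outcomes. The unit-level comparison needs no new data. The binomial model and the weighting depend on counts that the article does not confirm the trial holds.

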### Missing data

We will make every effort to minimize the amount of missing data. Trial enrollment and the fidelity of follow-up procedures will be reviewed during biweekly conference calls. A study biostatistician will produce frequency reports to assess for missing data, and the study team will troubleshoot any problems encountered. We will report the rates of missing data for each outcome by study arm.

### Safety and monitoring

This study does not pose any potential harm to care team staff or their patients and all current procedures at the sites for the care teams will continue to be used. All participating staff have given consent. They may withdraw at any time with no impact on their position in the health system.

## Discussion

Transforming primary care delivery is a key priority in the United States for addressing population health management. Providing care with a team-based approach has been proposed and evaluated as a solution for primary care. To the best of our knowledge, there is no empirical evidence on the role of team-based care in improving patient safety, patient centeredness, and health outcomes. The formation of a team alone cannot guarantee success. There are many methodological proposals on proper team implementation and some include training for the team members. We propose that giving the leaders (physicians, nurses, and administrators) skills they can implement within the daily huddles of their care teams, concentrating specifically on communication and problem-solving skills, will directly impact and improve the quality of teamwork.

Our aim is to evaluate the effectiveness of our intervention on team morale, clinician burnout, patient satisfaction, and quality of care. Our cluster randomized trial has been designed to test the impact of the training on leadership and problem-solving skills within daily huddles in the context of primary care. Our inclusion criteria cover many sites meeting the needs of a broad range of populations.

This trial is being implemented within routine care. The demands of busy practices may cause logistical problems. The ability of each care team to continue to huddle every day and the participation of the intervention arm in the training and the continued activities of the intervention (biweekly phone calls with a trainer and the visit after 100 days by a trainer) may differ by care team. Staff turnover within primary care causes additional challenges, in that the team dynamic is affected along with loss of information and time that goes into training new personnel.

The evaluation of the outcomes of the trial will allow us to explore the impact of the training and the ability of the care teams to implement huddles within primary care. If the intervention is proven to be successful, it will be implemented in standard care sites on their request. The implementation strategy for the intervention will be assessed in this setting, as we will need to assess the impact on the care teams. All study results will be presented to the Mayo Clinic Health System on completion and the results will be published.

### Trial status

In total, 30 care teams responded to the email invitation to participate. The 30 care teams consisted of 23 unique randomizing units due to staff overlap. Post-randomization prior to the baseline surveys being sent out, one unit that had one care team and another two care teams withdrew from participation. Excluding the care team that withdrew, 11 units were randomized to the intervention arm (13 care teams) and 11 to usual care (16 care teams). The retreat took place on 13 April 2017. Data collection is still ongoing.

## Abbreviations

AHRQ: US Agency for Healthcare Research and Quality
CMS: Centers for Medicare and Medicaid Services
IRB: Institutional Review Board
